## Abstract

**Introduction:**

Early life soil-transmitted helminth infection and diarrhea are associated with growth faltering, anemia, impaired child development, and mortality. Exposure to fecally contaminated soil inside the home may be a key contributor to enteric infections, and a large fraction of rural homes in low-income countries have soil floors. The objective of this study is to measure the effect of installing concrete floors in homes with soil floors on child soil-transmitted helminth infection and other maternal and child health outcomes in rural Bangladesh.

**Methods and analysis:**

The Cement-based flooRs AnD chiLd hEalth (CRADLE) trial is an individually randomised trial in Sirajganj and Tangail districts, Bangladesh. Households with a pregnant woman, a soil floor, walls that are not made of mud will be eligible, and no plan to relocate for 3 years. We will randomise 800 households to intervention or control (1:1) within geographic blocks of 10 households to account for strong geographic clustering of enteric infection. Laboratory staff and data analysts will be blinded; participants will be unblinded. We will install concrete floors when the birth cohort is in utero and measure outcomes at child ages 3, 6, 12, 18, and 24 months. The primary outcome is prevalence of any soil-transmitted helminth infection (*Ascaris lumbricoides, Necator americanus*, or *Trichuris trichiura*) detected by qPCR at 6, 12, 18, or 24 months follow-up in the birth cohort. Secondary outcomes include household floor and child hand contamination with *E. coli*, extended-spectrum beta-lactamase producing *E. coli*, and soil-transmitted helminth DNA; child diarrhea, growth, and cognitive development; and maternal stress and depression.

**Ethics and dissemination:**

Study protocols have been approved by institutional review boards at Stanford University and the International Centre for Diarrheal Disease Research, Bangladesh (icddr,b). We will report findings on ClinicalTrials.gov, in peer-reviewed publications, and in stakeholder workshops in Bangladesh.

**Trial registration number:**

NCT05372068, pre-results

## Introduction

The United Nations has enshrined basic housing as a human right, and housing improvements are associated with improved health (Thomson et al. 2009; Thomson, Sellstrom, and Petticrew 2013). Yet, 58.8% of homes in low-income countries are unimproved, with soil floors and walls (Morakinyo, Fagbamigbe, and Adebowale 2022) made of palm or thatch, and few studies have investigated health benefits of housing upgrades in low- or middle-income countries (LMICs). In low-income homes, inadequate sanitation infrastructure can result in contamination of household soil and surfaces with human and animal feces. In particular, soil floors are a reservoir for enteric pathogens such as soil-transmitted helminths (STH), *Shigella*, and pathogenic *E. coli* (Steinbaum et al. 2019, 2016; Shrivastava et al. 2020). Multiple studies have found that the amount of *E. coli* and STH is similar or higher on soil floors inside the home than on latrine floors (Steinbaum et al. 2016; Pickering et al. 2012; Schulz and Kroeger 1992). *Ascaris lumbricoides* eggs are extremely hardy and can survive for years in soil; other STH species can survive for weeks or months (S. Brooker, Clements, and Bundy 2006; Ransom and Foster 1920). Soil is also a reservoir of antimicrobial resistant pathogens because microorganisms in soil can exchange genes with those in feces deposited on soil (Zhu et al. 2019). Children frequently play, eat, and drink on floors that are contaminated with human or animal feces, and young children frequently ingest soil, increasing their risk of infection with STH, other enteric pathogens, and antimicrobial resistant pathogens (Kwong, Ercumen, Pickering, Arsenault, et al. 2020; Kwong, Ercumen, Pickering, Unicomb, et al. 2020; Goddard et al. 2020; Ercumen, Pickering, et al. 2018; Ercumen, Mertens, et al. 2018; Fuhrmeister et al. 2020; Pickering, Swarthout, et al. 2019; Kwong et al. 2021).

Collectively, enteric infections, including STH and diarrhea, are a major contributor to the global burden of disease. They were the third leading cause of death for children <5 years in 2019 (“Global Burden of Disease” 2019). Chronic STH infection is associated with an increased risk of child wasting, anemia, dysentery, intestinal obstruction, impaired child development, and mortality (Simon Brooker, Bethony, and Hotez 2004; Jourdan et al. 2018). Hookworm infection alone is responsible for up to $139 billion in annual productivity losses globally (Bartsch et al. 2016). In addition to increased risk of mortality, early life diarrhea is associated with growth faltering, anemia, and impaired child development (Pinkerton et al. 2016; Lorntz et al. 2006; Niehaus et al. 2002; Kotloff et al. 2013; MacIntyre et al. 2014; MAL-ED Network Investigators 2017; Kosek and MAL-ED Network Investigators 2017).

Existing interventions to reduce enteric infections, such as water, sanitation, and hygiene (WASH), do not address soil exposure, and a recent meta-analysis found that low-cost household WASH interventions did not reduce enteric pathogen prevalence in household soil samples (Mertens et al. 2023). Further, WASH interventions require sustained behavior-change promotion, which limits scalability (Pickering, Null, et al. 2019). In addition, recent WASH trials had only modest effects on diarrhea and mixed effects on STH infections (Pickering, Null, et al. 2019; Vaz Nery et al. 2019). Alternative interventions that reduce environmental pathogen reservoirs and do not require sustained behavior change are urgently needed to improve child health in LMICs.

Installing finished floors, such as concrete, in homes with soil floors is a promising potential intervention to reduce child enteric infection. Concrete floors are easier to keep clean than soil floors, which may contribute to lower levels of fecal pathogens on surfaces, and subsequently on hands and fomites. Concrete may also interrupt the life cycle of STH, which require soil to reach their infective stage (S. Brooker, Clements, and Bundy 2006). A recent meta-analysis of observational studies estimated that the odds of any enteric or parasitic infection was 0.75 times lower and the odds of helminth infections was 0.68 times lower in homes with improved floors (e.g., concrete, wood) vs. unimproved floors (e.g., soil) (Legge, Pullan, and Sartorius 2023). In addition, studies have found protective associations between improved floors and diarrhea (Koyuncu et al. 2020; Cattaneo et al. 2009).

By making homes more comfortable and easier to keep clean, floor upgrades can also improve quality of life and reduce stress. A study in Mexico found that installing concrete floors was associated with 10.6% lower stress, 12.5% lower depression, and 18.7% higher satisfaction with quality of life among mothers (Cattaneo et al. 2009). Slum upgrades, including concrete or wood floor installation, have been found to improve sleep, quality of life, and happiness (Galiani et al. 2017; Simonelli et al. 2013). Though findings from these studies are promising, all prior research has been observational, and associations may be confounded by household wealth.

Concrete floors could also influence child development through either an environmental pathway or maternal pathway (Figure 1). In the environmental pathway, installing concrete floors removes the majority of soil from the home’s interior and makes the home easier to clean, reducing child exposure to enteric pathogens, likely also reducing enteric infections, which are associated with impaired child development (Guernier et al. 2017; Grenham et al. 2011; Scharf, Deboer, and Guerrant 2014). In the maternal pathway, if concrete floors make the living environment more comfortable and easier to clean, this may result in increased maternal bandwidth (Mullainathan and Shafir 2013) – the ability to problem solve, recall information, reason logically, plan and allocate attention and initiate and control actions (Schilbach, Schofield, and Mullainathan 2016). Higher levels of maternal working and short-term memory are independently associated with maternal scaffolding behaviors when interacting with young children (Obradović et al. 2017, 2016). These scaffolding behaviors are associated with child cognitive skills at age four years (Obradović et al. 2016). Further, by reducing the time required to clean floors, concrete floors may increase mothers’ discretionary time. This may increase their ability to seek medical care and/or devote time to preventive health behaviors for themselves or their children, and engage in scaffolding behaviors that promote child development (Hyde, Greene, and Darmstadt 2020).

### Objectives

Here, we describe the protocol for the Cement-based flooRs AnD chiLd hEalth (CRADLE) trial, a randomised trial in Sirajganj district, Bangladesh to determine whether concrete floors reduce child STH infection and diarrhea. Using a randomised design will minimize confounding that may have influenced prior observational studies. We will investigate the mechanism through which concrete floors influence health using rich environmental assessments, video observations of child activities, and biopsychosocial measurements of mothers. Our longitudinal design will allow us to investigate sustainability over 2 years and capture any variation in intervention impact as children learn to sit, crawl, walk and spend more time outdoors and their exposures change. Cost-effectiveness analyses incorporating maternal and child outcomes will inform decisions about whether to scale up concrete floor installation. This study will generate rigorous evidence to inform policies about whether concrete floors should be delivered as a health intervention in rural, low-income settings.

## Methods and analysis

### Study design

The CRADLE trial is an individually randomised trial in Sirajganj and Tangail districts, Bangladesh. The trial will enroll households with soil floors and a pregnant woman in her second or third trimester. For each block of 10 geographically contiguous households, we will randomise households 1:1 to intervention or control. We will install concrete floors when the birth cohort is in utero so that children in the intervention arm receive the intervention from birth. We will measure outcomes longitudinally when children are aged 0, 3, 6, 12, 18, and 24 months (Figure 2). While STH prevalence is generally higher among primary school-aged children, we chose to focus on the first two years of life, when children’s exposure to household floors is greatest. Between 6 and 24 months, children frequently sit, play, crawl, and eat on household floors and generally spend more time inside vs. outside the home. After this age, children’s outdoor exposures increase; while household concrete floors may still benefit older children, we expect that potential effects would be smaller. Additionally, the first 1000 days of life are considered critical for child development and therefore present an important window for health interventions (Victora et al. 2021).

### Study site

Our study site is located in Chauhali and Belkuchi upazilas (sub-districts) in Sirajganj district and Nagarpur upazila in Tangail district, Bangladesh (Figure 3). Chauhali upazila is approximately 210 km^2^ and includes 34,449 households, Belkuchi upazila is approximately 164 km^2^ and includes 96,110 households, and Nagarpur upazila is approximately 267 km^2^ and includes approximately 83,885 households (“Population and Housing Census 2022, National Report” 2023, “Bangladesh National Portal,” n.d.). Research staff from the International Centre for Diarrhoeal Disease Research, Bangladesh (icddr,b) will enroll households in all unions of Chauhali and Belkuchi and unions adjacent to Chauhali in Nagapur. Approximately 66% of households in our study area have mud floors, and the region is vulnerable to flooding and erosion (“Nationwide Climate Vulnerability Assessment in Bangladesh” 2018; Ali et al. 2017). According to the Chauhali Upazila Health & Family Planning Office, there is a high percentage of open defecation in this region, and clinical diagnoses of soil-transmitted helminth (STH) infections are common. The primary STH control strategy in Bangladesh consists of a biannual school-based deworming campaign whereby a single dose of mebendazole is administered to school-aged children (Hafiz et al. 2015; Gerber et al. 2023).

### Inclusion and exclusion criteria

We will enroll households if they have floors made entirely of soil or earth and if there is a pregnant woman at 14-30 weeks of gestation at the time of enrollment. Pregnancy status will be self-reported. Primary outcomes will be measured in the child (or children, in the case of multiples) born to enrolled women (i.e., “index children”). We will exclude households with plans to relocate within 3 years or pregnant women who will be leaving their homes for child delivery for more than three months. Additionally, we will exclude households with mud walls as installing concrete floors may reduce structural stability.

### Outcomes

Our primary outcome is the prevalence of any of the following STH infections, *Ascaris lumbricoides, Necator americanus, or Trichuris trichiura*, detected using qPCR in child stool at 6, 12, 18, or 24 months after the birth of the index child. Secondary outcomes include the prevalence of each STH species by qPCR at child ages 6, 12, 18, or 24 months and caregiver-reported diarrhea in the past 7 days and diarrhea confirmed using stool consistency (Lane et al. 2011) at each follow-up. Additional secondary outcomes are listed in Table 1.

### Sample size calculation

The overall trial sample size was determined based on the primary outcome of prevalence of any STH at any follow-up (ages 6, 12, 18, 24 months). We estimated the required sample size using the standard formula for comparisons of two groups with repeated measures of a binary outcome (Liu and Liang 1997). From 2017-2020 in Sirajganj District, prevalence of *Ascaris lumbricoides* was 25.1%, and prevalence of *Trichuris trichiura* was <10% (Gerber et al. 2023). To be conservative, we assumed the prevalence of any STH in the control group over four follow-up rounds would be 20%. In our prior analyses of the association between concrete floors and any STH, the unadjusted prevalence ratio was 0.40 (95% CI 0.28, 0.56) (Benjamin-Chung et al. 2021), and the adjusted prevalence ratio was 0.73 (95% CI 0.52, 1.01) (Benjamin-Chung et al. 2015). We assumed a minimum detectable prevalence ratio of 0.70. We assumed intraclass correlation = 0.066 for repeated measurements of STH prevalence among children < 2 years (Platts-Mills et al. 2015). Assuming a Type I error = 0.05 and Type II error = 0.20, for a two-sided hypothesis test, the required number of households per arm is 336. Inflating this to account for 15% loss to follow-up and 10 households per randomisation block, the total required sample size across both arms is 800. 15% loss to follow-up was assumed based on the findings from the prior trial carried out by our team in rural Bangladesh (Luby et al. 2018), in which 6.5% of pregnant women miscarried or had still births, 3.5% of children died by 12-month follow-up, and <1% died between 12-24 months follow-up.

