**Figure 3. F3:**
[figure not shown]
CRADLE Study site map A) Map of study site location within Sirajganj and Tangail districts, Bangladesh. B) Exterior boundary of unions included in the study site in Chauhali, Belkuchi, and Nagarpur unions of Sirajganj and Tangail districts. Base map source: Esri.

**Table 1. T1:** Outcome measures

Primary outcome	
Prevalence of any soil-transmitted helminth using qPCR	Proportion of children in which *Ascaris lumbricoides, Necator americanus, or Trichuris trichiura* was detected in stool by qPCR at any follow-up measurement (6, 12, 18, or 24 months of age).
Secondary outcomes	
*Child health outcomes*	
Prevalence of *Ascaris lumbricoides, Necator americanus* or *Trichuris trichiura* using qPCR	Proportion of children in which *Ascaris lumbricoides, Necator americanus* or *Trichuris trichiura* was detected in stool by qPCR at any follow-up measurement (6, 12, 18, or 24 months of age).
Mean *Ascaris lumbricoides, Necator americanus* and *Trichuris trichiura* eggs per gram	Geometric and arithmetic mean of *Ascaris lumbricoides, Necator americanus* and *Trichuris trichiura* eggs per gram detected in stool by Kato-Katz at any follow-up measurement (6, 12, 18, or 24 months of age)
Diarrhea prevalence	Prevalence of caregiver-reported and stool consistency based child diarrhea in the past 7 days (at least three loose or watery stools within 24 hours or at least one bloody stool) at any follow-up measurement (6, 12, 18, or 24 months of age)
Relative abundance and diversity of human pathogens	Human pathogens detected in child stool using shotgun metagenomic sequencing each follow-up round
Relative abundance and diversity of antimicrobial resistance genes	Antimicrobial resistance genes detected in child stool using shotgun metagenomic sequencing each follow-up round
*Child behavior*	
Rate of child soil contact and ingestion	Mean number of soil contact and ingestion events per child-hour observed during 6-hour video observations at each follow-up (6, 12, 18, 24 months)
*Child development outcomes*	
Mean ASQi score at 12 and 24 months	Mean communication, fine motor, gross motor, problem solving, personal-social and combined scores measured using the Ages and Stages Inventory calculated separately at 12 months and 24 months
Mean overall Family Care Indicator score at 12 and 24 months	Mean Family Care Indicator score overall measured separately at 12 months and 24 months (range: 0-3)
*Maternal outcomes*	

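### The stated sample-size inputs give about 184 households per arm, not 336; the paragraph contradicts itself and does not show which figure is wrong

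*Protocol article*

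**What the plan says.** The Sample size calculation section bases the size on "prevalence of any STH at any follow-up (ages 6, 12, 18, 24 months" and names a standard two-group formula for repeated measures of a binary outcome. Its inputs are:

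- Control prevalence: "we assumed the prevalence of any STH in the control group over four follow-up rounds would be 20" per cent.
- Effect: "We assumed a minimum detectable prevalence ratio of 0.70".
- Correlation: "We assumed intraclass correlation = 0.066 for repeated measurements of STH prevalence among children < 2 years".
- Error rates: "Assuming a Type I error = 0.05 and Type II error = 0.20, for a two-sided hypothesis test".

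The result is that "for a two-sided hypothesis test, the required number of households per arm is 336". Only after this does the section inflate for 15% loss to follow-up and for blocks of 10 households, reaching 800 in total. No other design effect or input is given for the 336.

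The Statistical analysis section plans generalized estimating equations (GEE) with an exchangeable correlation matrix for repeated measures within the child. Table 1 defines the primary outcome as the proportion of children in whom any of the three species "was detected in stool by qPCR at any follow-up measurement (6, 12, 18, or 24 months of age").

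**The concern.** With a low within-child correlation, four measurements per child carry much more information than one, so the number of children needed should fall to well under half of the single-measurement number. The printed 336 is more than half of it. Either an input or the result must differ from what was used.

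What is at stake is how the primary result is read. The section presents PR 0.70 as the smallest effect detectable with 80% power. If the printed ICC and four rounds are right, the trial can detect a weaker effect, and a null result would say more than the protocol implies. If a higher correlation was used, the 0.70 stands, but the ICC printed and attributed to a cited study is not the one behind the calculation.

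**Working it through.** **Inputs (Sample size calculation section).** p1 = 0.20; p2 = 0.70 × 0.20 = 0.14; m = 4 rounds; ρ = 0.066; two-sided 5%, so z = 1.960; 80% power, so z = 0.8416. Allocation is 1:1 (Randomisation section).

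**Step 1: the part that reproduces.** 2 × 336 = 672; 672 / 0.85 = 790.6, which rounds up to 800 in blocks of 10. The inflation is sound, so the fault lies in 336 or in something that feeds it.

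**Step 2: one measurement per child.**
n₁ = (1.960 + 0.8416)² × [p1(1−p1) + p2(1−p2)] / (p1−p2)²
= 7.849 × (0.1600 + 0.1204) / 0.0036 = 611.3 per arm.

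**Step 3: four exchangeable measurements per child.**
Factor = [1 + (m−1)ρ] / m = (1 + 3 × 0.066) / 4 = 0.2995.
n = 611.3 × 0.2995 = 183.1, so 184 per arm. The ratio 336 / 183.1 is 1.84.

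**Step 4: does the choice of formula explain the gap?** All rows use m = 4 and ρ = 0.066.

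| Version | One measurement | Four rounds |
|---|---|---|
| Unpooled variance | 611.3 | 183.1 |
| Pooled variance | 615 | 184.2 |
| Log odds ratio | 620.8 | 185.9 |
| Log prevalence ratio | 625.8 | 187.4 |
| Continuity-corrected | 647 | 193.8 |
| Control variance in both arms | 697.7 | 209.0 |
| 90% power instead of 80% | 822 | 246.2 |
| 0.70 read as an odds ratio | 866 | 259.4 |

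The last two rows already depart from the stated inputs. Applying a block design effect of 1 + 9 × 0.066 = 1.594 to 184 gives 293. None of these reaches 336.

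**Step 5: what would give about 336?**

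- Four rounds with a higher correlation: ρ = (4 × 336 / n₁ − 1) / 3. This is 0.399 (unpooled), 0.395 (pooled) or 0.383 (log PR). As a check, 611.3 × (1 + 3 × 0.40) / 4 = 611.3 × 0.55 = 336.2.
- Two measurements per child at ρ = 0.066: factor (1 + 0.066) / 2 = 0.533, giving 611.3 × 0.533 = 325.8 (unpooled) to 625.8 × 0.533 = 333.6 (log PR).
- Four rounds at ρ = 0.066 with control prevalence of about 0.12, or with a PR of about 0.774.

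**Step 6: consequences at 340 evaluable per arm (400 × 0.85).**

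- If ρ = 0.066 and four rounds are right, the effective number per arm is 340 / 0.2995 = 1,135. Power for PR 0.70 is about 97%, and the PR detectable with 80% power is about 0.78.
- If ρ is about 0.40 with four rounds, the effective number is 340 / 0.55 = 618. Power for PR 0.70 is about 80%, with almost nothing to spare.

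**The case against.** The best defence is that nothing in the trial's conduct depends on this. On the printed inputs the size is generous; with a correlation near 0.40 the planned power holds. Neither case alters enrolment or the planned analysis, and the step to 800 is correct. That stands, and it limits the point to a correction of the stated calculation. It does not make the paragraph right, because the section gives a complete set of inputs and a result that does not follow from them. A fuller protocol could explain the figure but would not repair this text.

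Three stronger readings are tempting, and the article does not support them.

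- *A reader might infer that an ICC of 0.40 was used.* That value is back-solved and appears nowhere in the article. It shifts with the variance form, and two measurements per child at 0.066 come close without it.
- *A reader might infer that the stated power and detectable PR are wrong.* They are wrong if 0.066 and four rounds are right. If only the printed ICC is wrong, both stand.
- *A reader might infer from Table 1 that each child contributes one ever-positive indicator with 20% in controls.* That would need about 612 per arm and leave about 55% power at 340. But the repeated-measures formula, the within-child ICC and the planned GEE all point to observations by round. This is a separate question about outcome wording and does not explain 336.

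Nor does the article tie its subsample sizes or secondary outcomes to this ICC, so no knock-on error there is shown.

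**Conclusion.** The point holds as an internal inconsistency. The stated inputs require about 184 households per arm (183 to 194 across standard two-sided, 80%-power formulas; 209 on a deliberately cautious variance), against a printed 336. Which figure is wrong cannot be settled from the article.

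This rests on three assumptions: the usual exchangeable-correlation factor for four complete rounds, which matches the planned GEE; 20% read as per-round prevalence; and no unstated design effect inside the 336. On the printed inputs the error is conservative, so the trial is not shown to be underpowered.

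**What to change.** Leave enrolment at 800 and correct the paragraph:

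1. State the ICC and the number of measurements per child actually used to obtain 336, and confirm that 20% is the prevalence at each round.
2. If 0.066 and four rounds are right, replace 336 with about 184 per arm required. Add that 340 evaluable per arm gives about 97% power for PR 0.70 and a minimum detectable PR of about 0.78.
3. If a higher correlation was used, correct the printed ICC and give its source. The 336 per arm and 80% power for PR 0.70 then stand, with a note that there is almost no slack.
4. If fewer measurements per child or another input was used, print that input and the result that follows from it.

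The input should come from the record of the original calculation and should not be chosen afterwards to fit 336. The cost is a few sentences of corrected text, with no change to recruitment, data collection or analysis.
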